### Joint Motion and Muscle Strength

#### Range of Motion (ROM)

Bilateral active knee and thoracolumbar spinal ROM in the sagittal plane will be measured using a universal long-arm goniometer and gravity-dependent bubble inclinometry. Active knee flexion and extension will be measured in the supine position, with the hip at 0° of extension, 0° of abduction/adduction, and 0° of internal/external rotation using a Baseline^®^ transparent plastic goniometer (Fabrication Enterprises, White Plains, NY, USA). The axis of the universal goniometer will be placed at the lateral femoral epicondyle. The stationary arm will be aligned with the greater trochanter along the proximal femur, and the moving arm will be aligned with the lateral malleolus along the distal tibia. Active flexion and extension of the lumbar spine will be measured using a Baseline^®^ bubble inclinometer (Fabrication Enterprises, White Plains, NY, USA) according to modified guidelines by Waddell et al.(107) The anatomical reference points for placing a bubble inclinometer to measure cervical flexion and extension are the C7 spinous process and the intervertebral space between the L2/L3 spinous processes. Participants’ starting position will be with their arms at their sides and their feet approximately shoulder-width apart(108). Participants will be instructed to bend forward to touch their toes or lean back as far as possible to assess active end-range thoracolumbar flexion and extension.

#### Motion Analysis

Marker-based motion capture will be used to quantify kinematic (joint and segmental motion) and kinetic (mechanical loading) during a standardized battery of evocative movement tasks. We will use marker-based motion capture (stereophotogrammetry) in an instrumented gait analysis laboratory to measure the three-dimensional positions and orientations of the trunk, pelvis, thigh, shank (leg), and foot segments(109). We will use a modified Helen Hayes “obesity-specific” biomechanical model of the trunk, pelvis, and thigh segments(110). The marker set will include 35 spherical 9.5mm retroreflective markers applied to the following anatomical sites: right and left acromion, C7 vertebral spine, L2-L3 intervertebral space, bilateral anterior superior iliac spine, bilateral posterior superior iliac spine, bilateral greater trochanters, bilateral femoral condyles, bilateral lateral femoral condyles, bilateral tibial tuberosities, bilateral fibular heads, bilateral medial malleoli, bilateral malleoli, bilateral first metatarsal heads, bilateral second metatarsal heads, bilateral fifth metatarsal heads, and bilateral calcaneus. Rigid plates consisting of 3 markers will be taped to the thighs, shanks (lower legs), and the sacrum. Kinematic data will be collected at 100 Hz using 16 Qualysis infrared, video recording cameras (Miqus, Qualysis North America, Inc., Buffalo Grove, IL, USA). Kinetic data will be collected using Kistler force platforms (Kistler Instrumente GmbH, St. Joseph, MI, USA) embedded in a walkway at a sampling frequency of 1200 Hz. Three-dimensional coordinates of the retroreflective markers will be pre-processed in Qualysis Tracking Manager^™^ (Qualysis North America, Inc., Buffalo Grove, IL, USA). Kinematic models will be developed in Visual 3D^™^ (C-Motion, Germantown, MD, USA, v2024.08.3). Kinematic data will be filtered using a fourth-order, low-pass Butterworth filter with a cutoff of 6 Hz. Kinetic data will be filtered using a fourth-order low-pass Butterworth filter with a cutoff frequency of 25 Hz.

The movement testing battery will include bilateral seated knee extension, overground walking, picking up a weight from a step (object pick-up task), and a bilateral step-down task (Figure 3). Participants will be given scripted instructions in either English or Spanish on how to perform each movement task and will complete one practice trial before recording. Participants will perform knee flexion and extension while sitting on a stool for the seated knee extension task. The stool will be adjusted to the participants’ height to maintain 90 degrees at knee flexion with the thighs parallel to the floor. Two trials will consist of 5 repetitions per leg, and the average of each trial will be used in all statistical analyses. For the walking task, participants will perform 5 trials over a 13 ft (396.2 cm) walkway at their self-selected gait speed. Gait speed will be included as a covariate in statistical analyses because it is associated with weight or BMI(111). The average of 3 trials will be used for statistical analyses. For the object pick-up task, participants will pick up a 5-lb (2.27 kg) weight from a 6-inch (15.2 cm) step and return it to its original position. There will be 3 trials of this task, and the average will be included in statistical analyses. For the step-down task, participants will be asked to ascend and descend a 6-inch step with the same lower extremity. There will be 2 trials for each lower extremity, and the average across trials will be included in the statistical analyses. The primary kinematic variables to be analyzed are peak knee flexion and extension, and peak trunk flexion and extension, across all movement tasks. The primary kinetic variables to be analyzed are peak knee and trunk extension moments (N · m/kg). We will include additional kinematic and kinetic variables in our exploratory analyses. Participants will rate their PAR before the practice trial. Upon completion of the last trial of the movement task, participants will be asked to rate their pain immediately and 1 minute after task completion.

#### Muscle Strength

Bilateral quadriceps strength will be measured using handheld dynamometry (HOGGANS Scientific, LLC, Salt Lake City, UT, USA). The test position will be with participants seated, knees at 90 degrees of flexion. The dynamometer will be placed approximately 1–3 cm proximal to the medial and lateral malleoli, and the tester will administer the “break test,” in which a perpendicular force is applied at the end of the knee extension movement(112). Participants will be instructed to extend their knee and maintain that position against resistance for a 5-second hold(113). There will be two trials per leg, and the average across trials will be used for analysis.

#### Harms and Adverse Events

Research personnel directly involved in data collection will be responsible for managing and reporting study harms and adverse events. Serious adverse events are not anticipated, and the study underwent an Expedited Review as it met the criteria for minimal risk. Unanticipated harms and adverse events will be queried and non-systematically documented electronically or by telephone within 72 hours after data collection and reported by authorized research personnel. Classification and grading of the severity of harms and adverse events will be documented by the research personnel directly involved in data collection, with additional review and final classification by the Principal Investigator. All unanticipated harms and adverse events that occur during data collection will be documented in REDCap at the time of occurrence and reported to the IRB within 7 business days. Continued study participation after an unanticipated harm or adverse event will be determined by institutional guidance, clinical decision-making, and participants’ decisions to continue or withdraw from the study.

### Planned Statistical Analyses

Participant demographics, anthropometric data, clinical pain and movement data, and patient-reported outcomes will be reported for the entire study cohort at baseline and at 6 months post-surgery. We will use frequency analyses to determine the point prevalence of widespread pain (i.e., relative frequency) within the cohort at all time points. The proportion of participants who meet the CWP inclusion criteria at baseline will be calculated. We will use log transformations or arc-sin-square-root transformations, as appropriate, for proportion data. We will also evaluate whether changes in PAR are increasing, decreasing, or stable between baseline and 6 months post-surgery using trend analyses on record-level data. We will also conduct an initial repeated analysis of covariance (ANCOVA).

### Primary and Secondary Aims

The study's primary aim is to systematically characterize and quantify changes in PAR 6 months post-surgery. The secondary aim is to quantify changes in MEP at the same study endpoint. NPRS pain ratings will be averaged, and change scores (PAR _baseline_ – PAR _6M_) will be calculated at baseline and 6M post-surgery (primary study endpoint). Aggregate MEP scores will be analyzed at baseline and at 6 months post-surgery. Since data will be correlated due to repeated measures of pain-related outcomes within the same participant, we will apply mixed-effects models at the record level to evaluate longitudinal changes in PAR after bariatric surgery(114). This model accounts for differences in PAR slope before and after a specified time event. Previous studies from our group indicate differences in PAR slope between baseline and 3 months post-bariatric surgery, and between 3M and 24 months post-surgery(115).

### Sensitivity Analyses and Missing Data.

To evaluate how biases and assumptions might influence the study results, we will perform pre-planned sensitivity analyses. Data will be examined visually and statistically for normality using Q-Q plots and Shapiro-Wilk tests. Data quality will be monitored throughout the study to detect patterns of missingness among primary, secondary, and exploratory variables. Missing data patterns will be analyzed using the appropriate statistical tests based on the variance between and within imputations relative to the total variance. If data are found to be completely missing at random, we will use multiple imputation methods to assess the impact of missing data on our analyses. We will report the number and percentage of missing values for all variable types. Attrition bias will be evaluated by comparing participants with and without baseline missing data to identify patterns in demographic and other variables. Additionally, we will ask participants for their reasons for withdrawal, if possible. To analyze subgroup differences in primary, secondary, and exploratory variables across multiple time points, we will use the False Discovery Rate (FDR) correction and the Benjamini-Hochberg procedure to control for multiple comparisons(116).

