### Sample Size Determination

The sample size needed to achieve the study's primary aim was determined using extant clinical data from a longitudinal observational cohort study of surgical weight loss(43) (NYU IRB# 16–01995). The primary objective of the study is to characterize and quantify changes in pain at rest (PAR, primary outcome) and MEP (secondary outcome). Power analyses were conducted based on the anticipated within-person mean change in pain at rest from baseline to 6 months post-surgery (primary outcome). Additionally, the clinical assumptions supporting our sample size determinations were the minimum clinically important difference (MCID) for the Brief Pain Inventory (BPI) average pain (2.1 points) and BPI Severity (2.2 points) scores in adults with fibromyalgia (44). The sample size was calculated to detect a Cohen’s d of 0.50 for BPI Severity scores at 3 months, based on a secondary analysis of the parent study cohort, which revealed a sharp reduction in pain intensity ratings in a stratified cohort of NHB and/or Hispanic/Latino/a/X/e adults(22). We considered a 1-point reduction in pain interference at 6 months to be conservative, as proposed in the Initiative on Methods, Measurement, and Pain Assessment in Clinical Trials (45). The sample size calculation assumed a Type I error rate of 2.5% to account for multiple comparisons and 90% power. We estimated a sample size of 50 using a two-sided paired t-test. Thus, we will recruit at least 60 participants to account for a 20% attrition rate, although attrition in the target study population may be higher(46).

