There are also limitations. Selection bias refers to systematic factors that can result in the misrepresentation or underrepresentation of the relationship between exposure and outcome(s) in a target study population(125), and can occur at any point from study enrollment to analysis(126). Study attrition among minoritized populations poses a challenge for observational longitudinal studies and may contribute to selection bias. Limited work-schedule flexibility, difficulty finding childcare, long commutes, and strained financial resources significantly hinder retention in weight-loss studies (127). Based on our previous work, we estimate a study attrition rate of 20–40% at the 6-month follow-up (22, 34). We acknowledge potential threats to the study's internal validity, such as bias and confounding, that may arise directly or indirectly from study attrition (128). The research team will mitigate attrition bias by approaching and screening all eligible patients for bariatric surgery. Since the majority of patients attending the bariatric surgery clinics at both sites are Spanish-speaking or bilingual (fluent in English and Spanish), our research team will communicate with prospective participants in their preferred language for receiving health information. Additionally, we will continually evaluate and implement best practices for recruiting and retaining study participants in weight management studies(129). Measurement bias can arise from systematic errors in data collection and from respondents’ understanding of and willingness to answer survey items, which may influence scoring and the clinical interpretation of the measurement tool (130). To mitigate measurement bias, we will use validated surveys in participants’ preferred language. Additionally, the research team will review participant surveys upon request and will periodically perform data validation to monitor for missing item responses and ensure data quality. A better understanding of the primary driver(s) of CWP dimensions and the key drivers of the intervention response to surgical weight loss could help identify pain responders and non-responders after weight loss who would significantly benefit from adjuvant analgesic or non-pharmacological interventions for continued pain relief during the postsurgical period.

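### The missing-data rules are mis-specified: imputation is tied to data being missing completely at random, and attrition bias is judged by baseline missingness rather than by loss of the 6-month visit

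*Protocol article*

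**What the plan says.** The protocol article, under Sensitivity Analyses and Missing Data, fixes three rules.

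- **When to impute:** "If data are found to be completely missing at random, we will use multiple imputation methods to assess the impact of missing data".
- **How to diagnose the pattern:** "Missing data patterns will be analyzed using the appropriate statistical tests based on the variance between and within imputations relative to the total variance".
- **How to check attrition bias:** "Attrition bias will be evaluated by comparing participants with and without baseline missing data to identify patterns in demographic and other variables".

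The section also promises monitoring of missingness, counts and percentages of missing values, and reasons for withdrawal where they can be had. It refers to pre-planned sensitivity analyses but describes none for non-random dropout.

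On the expected scale, the Discussion states: "we estimate a study attrition rate of 20–40% at the 6-month follow-up". It adds: "Study attrition among minoritized populations poses a challenge for observational longitudinal studies and may contribute to selection bias". Sample Size Determination allows for the lower end only: "Thus, we will recruit at least 60 participants to account for a 20% attrition rate".

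On the analysis itself, Primary and Secondary Aims calculates change scores in pain at rest (PAR) from baseline to 6 months and also applies record-level mixed-effects models. Exploratory Aim starts from bivariate correlations of percentage total weight loss (%TWL) with pain change, then uses generalized linear mixed models. The Data Collection overview places pain questionnaires and health surveys at 3 months. The Visit 1 tests, including sensory testing, physical function and motion capture, are repeated only at 6 months.

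**The concern.** Each of the three rules is wrong as written; none is merely short on detail.

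- **The imputation trigger is reversed.** If data are missing completely at random (MCAR), completers are a random subset and their mean is already unbiased. Imputation matters when missingness depends on observed data (MAR), and the rule does not invoke it there. MCAR also cannot be found from data. A test can only fail to reject it, and with about 60 participants such a test has little power.
- **The diagnostic does not diagnose.** Between- and within-imputation variances exist only after imputation and measure how much information was lost, not why. The rule is also circular: imputation waits on a finding that itself needs imputation.
- **The attrition check splits the wrong groups.** Attrition is loss of follow-up. A participant lost by 6 months normally has complete baseline data, so dropouts and completers fall on the same side of the split.

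At stake is an overstated improvement if people with little early relief are the ones who do not return at 6 months.

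**Working it through.** **Scale of loss.** The missing-data rules carry no figure of their own to reproduce. The relevant figures are 60 recruited and 20–40% attrition:

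- at 20%: 60 × 0.80 = 48 completers, 12 lost
- at 40%: 60 × 0.60 = 36 completers, 24 lost

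**Illustration of bias. All inputs here are assumptions except the attrition range.**

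- Pain at baseline, 3 and 6 months: trivariate normal with means 5.5, 4.25, 4.25 and SD 2.5.
- Correlations: baseline–3 months 0.5, baseline–6 months 0.5, 3–6 months 0.6.
- True 6-month change: 4.25 − 5.5 = −1.25. The SD of change is 2.5 × √(2 × (1 − 0.5)) = 2.5, so this is 0.50 SD.
- Dropout before 6 months: logistic in the baseline-to-3-month change, log-odds 0 (MCAR), 0.5 or 1.0 per SD, with the intercept set to give 20% or 40% loss.
- Overstatement = estimate ÷ (−1.25) − 1.

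Results with 1,000,000 simulated records:

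| Loss | Log-odds per SD | Completer mean change | Conditioning on baseline only | Conditioning on baseline and 3 months |
|---|---|---|---|---|
| 20% | 0 (MCAR) | −1.25 | −1.25 | −1.25 |
| 20% | 0.5 | −1.40 (about 11–12%) | −1.34 (7%) | −1.25 |
| 20% | 1.0 | −1.51 (21%) | −1.41 (13%) | −1.25 |
| 40% | 0 (MCAR) | −1.25 | −1.25 | −1.25 |
| 40% | 0.5 | −1.54 (23%) | −1.42 (14%) | −1.25 |
| 40% | 1.0 | −1.75 (40%) | −1.55 (24%) | −1.25 |

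The MCAR rows are where the plan would impute, and there is nothing to correct. In the other rows imputation would help, but the rule does not call for it.

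The last column represents imputation, or a likelihood model with unstructured covariance, that uses 3-month pain. In the same set-up a simpler random-intercept model gives −1.28 to −1.34, an overstatement of 2–7%. The baseline-only column represents any outcome measured only at Visits 1 and 3.

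**Other assumptions.** A second set used SD 2, a true reduction of 2.0 points and several correlation patterns.

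- Dropout driven by 3-month change (log-odds 1 per 2 points): completer reduction about 2.3 at 20% and 2.55 at 40%; MAR-based estimate 2.00.
- Dropout driven by 3-month pain level: completer reduction 2.07 and 2.13 with unequal correlations, but 2.00 with equal correlations, so no bias.
- Dropout driven by the unseen 6-month pain (missing not at random, MNAR): completer reduction 2.10–2.23 at 20% and 2.19–2.43 at 40%; MAR-based estimate 2.13–2.24 and 2.26–2.46. Neither is protected.

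**The case against.** The strongest reply is that a reader might infer from this section that the plan does nothing about informative dropout, and that inference is wrong. Primary and Secondary Aims plans record-level mixed-effects models for PAR, the primary outcome, and pain data are gathered at 3 months. Fitted by likelihood to all available records, such a model keeps participants who miss the 6-month visit and is valid under MAR without imputation. The table shows the bias disappearing, or nearly so, once 3-month pain is in the model. Imputation is offered only as a way to gauge the effect of missing data, so failing its trigger does not remove the main analysis. The plan also monitors missingness, asks for reasons for withdrawal and acknowledges attrition as a threat. All of this stands.

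It has limits:

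- The change scores are defined for completers only. So are the %TWL correlations, because %TWL is calculated at 6 months.
- Movement-evoked pain, sensory testing, objective function and biomechanics have no 3-month value, so their models can condition only on baseline.
- The article does not say clearly that the numeric rating scale used for PAR is among the 3-month questionnaires.
- No analysis is described for MNAR dropout.

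A second reply is that the text contains slips: MAR may have been meant for MCAR, and a comparison of baseline characteristics may have been meant for one by baseline missingness. That is possible, but the rules would still need correcting. MAR cannot be established from the observed data either, so making imputation conditional on finding it would not work.

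A third reply is that imputation covariates and sensitivity values belong in a statistical analysis plan. That is right, and their absence is not part of this point.

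**Conclusion.** The point holds in limited form and should be fixed. The imputation condition, the pattern test and the attrition comparison are each mis-specified, in a study that expects to lose 20–40% of participants by its primary endpoint.

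The 11–40% overstatement applies to completer mean change, and the 7–24% to two-visit outcomes adjusted for baseline only. Both rest on an assumed SD, assumed correlations and an assumed dropout model that the documents do not give, and under other assumptions the bias can be smaller or absent. Neither range should be read as the expected bias in the primary result: a likelihood mixed model using 3-month pain largely removes it for PAR, provided PAR is recorded at 3 months and dropout is MAR. That protection is why this falls short of a fault that invalidates the primary analysis.

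**What to change.** Delete the MCAR condition and the imputation-variance test, and replace the attrition sentence. Suggested wording:

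> MAR-based analysis will be done whatever the result of any MCAR test: a likelihood mixed model on all available baseline, 3-month and 6-month records for pain at rest, and multiple imputation using baseline and 3-month pain for change scores, correlations with weight loss, and outcomes measured only at Visits 1 and 3. Attrition bias will be assessed by comparing participants with and without the 6-month visit on baseline characteristics and 3-month pain. One sensitivity analysis will allow departure from MAR, for example by delta adjustment, with values set in the statistical analysis plan.

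The article should also state whether the numeric rating scale is collected at 3 months, since the protection for PAR depends on it.

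The cost is a change of wording and a few hours of extra programming. The analyses use measurements already scheduled, and recruitment is still open, so the change can be made before analysis.

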#### Ethics and Dissemination

The study was approved by the NYU Langone Health Institutional Review Board (Study #: i21–01652) and by NYC Health + Hospitals/Bellevue Office of Research (Bellevue Study ID #: STUDY00003739). All study procedures will be conducted according to principles outlined in the Declaration of Helsinki and in the International Council for Harmonisation (ICH) Integrated Addendum to ICH (R3) Guideline for Good Clinical Practice(117), as well as other institutional and municipal regulations. The study will undergo annual reviews and auditing upon request to ensure safety and compliance with federal regulations. All protocol amendments will be subject to approval by the NYU Langone Health Institutional Review Board and NYC Health + Hospitals/Bellevue Office of Research. Substantive study modifications will be communicated to currently enrolled participants in English or Spanish, and updates to trial registries will be made within 30 days of institutional approval.

Findings will be reported in accordance with the Strengthening the Reporting of Observational Studies in Epidemiology (STROBE) Guidelines for observational studies and the principles outlined in the Guiding Principles for Equity in Reporting (118, 119). Authorship eligibility will be determined in accordance with journal guidelines in advance of publication. Study results will be published in peer-reviewed journals and presented at national and international conferences, community events, to lived experience experts and health advocates, and on social media outlets. In collaboration with a subset of study participants who have completed the study and with NYC H+H/Bellevue providers, we will determine appropriate strategies for communicating study results in both English and Spanish to all study participants, health care providers, and the general public. The study team will identify methodologies and repositories most appropriate for data sharing and management in accordance with the FAIR Guiding Principles (120) and sponsor policies.

